# 1. Background and rationale

Chronic low back pain (CLBP) is the leading cause of disability worldwide and imposes a substantial health, social, and economic burden on individuals and healthcare systems. It affects more than 600 million people globally and contributes substantially to work absenteeism, reduced productivity, and reduced quality of life.

In Bangladesh, access to evidence-based rehabilitation remains limited despite the high burden of low back pain. Physiotherapy services are underutilised and are often shaped by treatment paradigms that emphasise electrotherapy as a standalone intervention rather than integrating it into active, evidence-based approaches. Although electrotherapy can be beneficial as an adjunct to rehabilitation, its isolated use may limit overall treatment effectiveness.

Shortwave diathermy (SWD) is widely used in physiotherapy practice in Bangladesh despite international guidelines generally classifying SWD as a low-value treatment for nonspecific low back pain because of inconsistent evidence regarding its effectiveness. In physician-led low back pain management pathways, physiotherapy is commonly recommended as part of the overall treatment strategy. The popularity of SWD among clinicians may be influenced by traditional training curricula, patient preference for heat-based pain relief, and limited local research evaluating its true clinical value.

Continuous shortwave diathermy (CSWD) delivers high-frequency electromagnetic energy to biological tissues and may produce thermal and physiological effects, including increased local circulation, reduced muscle spasm, improved connective tissue extensibility, and facilitation of tissue healing. However, the clinical relevance of these physiological effects in patients with CLBP remains uncertain.

Previous randomised controlled trials investigating SWD for low back pain have shown inconsistent results. Some studies have reported reductions in pain and improvements in function, while others have found no clinically meaningful benefit. These conflicting findings may be explained by small sample sizes, lack of sham control groups, variation in intervention protocols, and short follow-up periods.

Given the frequent use of SWD in Bangladesh and the uncertainty regarding its clinical effectiveness, a rigorous sham-controlled randomised trial is needed. This study aims to generate context-specific evidence regarding whether CSWD provides additional benefit when used as an adjunct to standard physiotherapy for patients with CLBP.

# 2. Objectives

## 2.1 Primary objective

To determine whether continuous shortwave diathermy combined with standard physiotherapy is more effective than sham shortwave diathermy combined with standard physiotherapy in reducing pain intensity and disability in patients with chronic low back pain.

## 2.2 Secondary objectives

1. To compare the effects of active CSWD and sham CSWD on psychosocial outcomes and sleep disturbance.
2. To evaluate treatment credibility and participant satisfaction.
3. To assess healthcare utilisation and participant global impression of change.
4. To determine whether CSWD provides clinically useful additional benefit as an adjunct to standard physiotherapy in a resource-constrained setting.

# 3. Study design

This study is a multicentre, two-arm, parallel-group, randomised, single-blind, sham-controlled clinical trial.

Participants will be randomly allocated in a 1:1 ratio to one of two groups: active CSWD plus standard physiotherapy, or sham CSWD plus standard physiotherapy.

Participants and outcome assessors will be blinded to treatment allocation. Treating physiotherapists cannot be blinded because active CSWD produces perceptible warmth.

Outcome assessments will be conducted at baseline, week 4, week 12, and week 24. The total follow-up period will be 24 weeks.

# 4. Study setting

The trial will be conducted at three tertiary-level hospitals or physiotherapy centres in Dhaka, Bangladesh:

1. Uttara Adhunik Medical College and Hospital
2. Asia Digital Physiotherapy & Orthopedic Rehabilitation Center
3. Japan Bangladesh College of Physiotherapy and Health Sciences

All participating centres will follow identical treatment, assessment, data-collection, and safety-monitoring procedures.

# 5. Recruitment period and study timeline

Recruitment is planned to begin in June 2026 and is expected to be completed by June 2027. The final 24-week follow-up assessment is expected to be completed by December 2027. Data cleaning, analysis, and interpretation are expected to be completed by June 2028.

Based on patient flow at participating centres, each centre is expected to identify approximately 10-15 potentially eligible patients with CLBP per week. Recruitment of 208 participants across three centres is therefore considered feasible within the planned recruitment period.

No participants have been enrolled at the time of protocol submission.

# 6. Participant characteristics

Participants will be adults aged 18-65 years with chronic nonspecific low back pain lasting at least three months. Participants may have low back pain with or without referred leg pain and must report an average baseline pain intensity of at least 4 on a 0-10 numerical rating scale. Both male and female participants will be eligible.

# 7. Eligibility criteria

## 7.1 Inclusion criteria

1. Age 18-65 years.
2. Male or female.
3. Diagnosis of chronic nonspecific low back pain persisting for at least three months.
4. Pain located between the 12th rib and inferior gluteal fold, with or without referred leg pain.
5. Average baseline pain intensity of at least 4 on a 0-10 numerical rating scale.
6. Ability and willingness to provide written informed consent.
7. Ability to attend treatment sessions and follow-up assessments.

## 7.2 Exclusion criteria

1. Red-flag conditions, including suspected fracture, tumour, infection, or cauda equina syndrome.
2. Previous spinal surgery.
3. Metallic implants or pacemaker.
4. Pregnancy.
5. Malignancy.
6. Ongoing structured physiotherapy or other investigational treatments for low back pain.
7. Cognitive impairment or inability to follow instructions.
8. Any contraindication to shortwave diathermy.

# 8. Screening and informed consent

Potential participants will be identified from outpatient physiotherapy and rehabilitation services at participating centres. Trained research staff will screen potential participants using the predefined eligibility criteria.

Eligible participants will receive verbal and written information about the study, including its purpose, procedures, potential benefits, potential risks, voluntary nature of participation, confidentiality, and right to withdraw at any time without penalty.

Written informed consent will be obtained before any study-specific procedure, baseline assessment, or randomisation is performed.

# 9. Randomisation and allocation concealment

Randomisation will be conducted using a computer-generated random allocation sequence. Permuted block randomisation with block sizes of 4 and 6 will be used and stratified by centre.

Allocation concealment will be maintained using sequentially numbered, opaque, sealed envelopes prepared by an independent researcher who is not involved in participant recruitment, treatment delivery, or outcome assessment.

After baseline assessment and informed consent, the treating physiotherapist will open the next sequential envelope to determine group allocation.

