# 10. Blinding

Participants and outcome assessors will be blinded to treatment allocation. Treating physiotherapists cannot be blinded because active CSWD produces a perceptible heating sensation.

To maintain participant blinding, both groups will receive identical positioning and device placement. Device appearance will be identical in both groups where possible. Participants in both groups will be informed that the perception of warmth varies between individuals.

At week 4, participants will be asked to guess their group allocation to assess blinding success.

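### The unblinded treating physiotherapist opens the envelopes in centre strata with disclosed blocks of 4 and 6, and the protocol requires neither separation from recruitment nor a log before opening, so allocations are partly predictable

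*Protocol*

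**What the plan says.** Section 9 of the protocol states: "Permuted block randomisation with block sizes of 4 and 6 will be used and stratified by centre". For concealment it specifies "sequentially numbered, opaque, sealed envelopes prepared by an independent researcher who is not involved in participant recruitment, treatment delivery, or outcome assessment". The opening is then given to a person who does deliver treatment. Once consent and baseline are done, "the treating physiotherapist will open the next sequential envelope to determine group allocation".

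Section 10 says of the same people: "Treating physiotherapists cannot be blinded because active CSWD produces a perceptible heating sensation". Section 3 says the same.

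On recruitment, Section 8 reads: "Potential participants will be identified from outpatient physiotherapy and rehabilitation services at participating centres". It adds: "Trained research staff will screen potential participants using the predefined eligibility criteria". It also requires written consent before baseline assessment or randomisation.

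The protocol does not say:
- whether the research staff who screen are separate from the treating physiotherapists;
- how many physiotherapists treat at each centre;
- who holds the envelopes, or who generated the sequence;
- whether anything is written on an envelope or logged before it is opened;
- whether the two block sizes come in random order, or are kept from the sites.

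**The concern.** Whoever opens an envelope learns that allocation, and an unblinded therapist also sees it in use. With small balanced blocks, past allocations carry information about the next one. The sequence is separate for each centre, so local knowledge is enough to exploit it.

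A therapist who can anticipate the next arm could influence who is put forward, or when. With no entry required before opening, an envelope could also be opened early or taken out of order, and nothing in the protocol would show it.

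There is room for this. Section 5 expects 10-15 potentially eligible patients per centre per week. Over three centres and about 52 weeks (assumed from the June 2026 to June 2027 window), that is 10 × 3 × 52 = 1,560 to 15 × 3 × 52 = 2,340 candidates for 208 places, so only about 9% to 13% are needed. Some eligibility criteria in Section 7 also need judgement, such as ability to attend sessions or to follow instructions.

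The primary outcomes in Section 13.1 are pain ratings and a disability index. The model in Section 17 contains group, time and their interaction. It could not remove selection on unmeasured prognosis.

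**Working it through.** The protocol gives no figure for predictability, so there is none to reproduce.

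**Inputs.** Block sizes 4 and 6, 1:1 allocation, three centre strata, total 208 (Sections 3, 4, 9 and 16). Assumed: equal recruitment, so 208/3 ≈ 69 per centre; and, where block order is random, each size with probability 1/2.

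**1. Guess the arm that is behind, toss a coin when level.** The arms are level at the end of every block, so this rule needs no knowledge of block sizes or boundaries. For a complete block of size b, the expected number of correct guesses is b/2 + ½ × [2^b / C(b, b/2) − 1].
- b = 4: 2 + ½ × (16/6 − 1) = 2.83
- b = 6: 3 + ½ × (64/20 − 1) = 4.10
- Together: (2.83 + 4.10)/10 = 69.3%

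Simulating 69 participants, where the last block may be incomplete, gives 69.0%. An observer who knows the sizes and updates the probabilities of block size and position after each allocation does no better on this measure (69.0%), but can predict about 48% of allocations with at least 75% confidence.

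**2. Allocations known with certainty.** If block order is known, so that both starts and sizes are known:
- Block of 4: the fourth is always certain. The third is certain when the last two are alike (probability 1/3). Sum 1.33.
- Block of 6: the sixth is always certain. The fifth is certain when the last two are alike (0.4), and the fourth when the last three are alike (0.1). Sum 1.5.
- Together: (1.33 + 1.5)/10 = 28.3%

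If the order is random and the observer must infer starts and sizes from the allocations, simulation gives 5.6%, a mean of 3.9 of 69 per centre (5th to 95th percentile 0 to 10).

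**3. Several therapists per centre.** Cases are split at random, and each therapist guesses from own cases only.

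| Therapists per centre, no sharing | Correct guesses |
| --- | --- |
| 1 | 69% |
| 2 | 54% |
| 3 | 53% |
| 4 | 52% |

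**4. Larger blocks.** For sizes 6, 8 and 10 the formula gives (4.10 + 5.33 + 6.53)/24 = 66.5%; simulation with 69 per centre gives 66.0%. Against the simulated 69.0%, the gain is about 3 percentage points.

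**The case against.** The strongest reply is that the protocol already has real safeguards. Envelopes are numbered, opaque, sealed and independently prepared. Opening follows consent and baseline assessment. Research staff screen against predefined criteria. Section 12 adds site supervision and steering committee oversight, and Section 18 has the committee supervise data integrity. Foreknowledge biases the comparison only if a therapist can affect referral, eligibility or the order of enrolment, or breaches the procedure. Several therapists per centre who share nothing would guess little better than chance.

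This stands as a limit on the size of the risk. It does not remove it: the protocol neither separates the screening staff from the treating physiotherapists nor bars sharing, and the supervision it describes is not tied to envelope handling.

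A reader might infer more than the text supports:
- **That the therapist holds the envelopes and has seen every earlier allocation at the centre.** Section 9 says only who opens them, and the number of therapists is not given.
- **That nobody independent controls release.** The protocol is silent on custody, and silence does not establish absence.
- **That the independent researcher generated the list.** Section 9 says this person prepared the envelopes.
- **That the disclosed sizes cause the 69%.** The simple guessing rule does not use them. Disclosure matters for the allocations that become certain.
- **That about 15% of allocations are certain.** This needs every block start to be known while its size is not: 1.5 certain allocations in a block of 6 and none in a block of 4, so 1.5/10. With mixed sizes in random order, an observer often cannot know the starts.
- **That independent release would make the next arm harder to guess.** The therapist still learns each arm. Release or logging guards against early opening and reordering only.

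**Conclusion.** The concern holds as a weakness in the allocation procedure. It is not evidence that concealment will fail. Allocations are partly predictable, by an amount that depends on facts the protocol does not give. The upper case is about 69% correct guesses against 50% by chance, and it assumes that one person sees, or is told, every allocation at a centre. The share known with certainty then runs from about 6% (random block order) to 28% (known order). With two to four therapists who do not share, guessing is about 52-54%.

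These figures measure predictability only. The protocol gives no basis for a figure on the resulting bias in the treatment effect, or on the chance of tampering. The routes that remain open are referral, timing, early opening and reordering. The change is worth making because it is cheap, and Section 5 says that nobody had been enrolled at protocol submission.

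**What to change.** 1. **Separate the roles.** In Sections 8 and 9, state that treating physiotherapists take no part in identifying, screening or enrolling patients. This limits what a good guess can be used for.
2. **Log before opening.** After consent and baseline, and before opening, require participant ID, date and time on the sealed envelope and in a log. The independent researcher checks the log against the sequence. Where feasible, that researcher could release each allocation instead. This step prevents or exposes tampering; it does not make the next arm harder to guess.
3. **Withhold the block details.** Move the block sizes to a document not available to site staff. Change them, since 4 and 6 are already disclosed, and state that they come in random order. Alone this achieves little: sizes of 6, 8 and 10 lower guessing only to about 66%.

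The cost is protocol wording and a small logging and checking burden. Release by the independent researcher would need someone reachable during clinic hours at three centres, which is a real demand on a trial without specific funding (Section 22). The logged envelope is the lighter option.

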# 10. Blinding

Participants and outcome assessors will be blinded to treatment allocation. Treating physiotherapists cannot be blinded because active CSWD produces a perceptible heating sensation.

To maintain participant blinding, both groups will receive identical positioning and device placement. Device appearance will be identical in both groups where possible. Participants in both groups will be informed that the perception of warmth varies between individuals.

At week 4, participants will be asked to guess their group allocation to assess blinding success.

# 11. Interventions

All participants will receive a standardised physiotherapy programme three times per week for four weeks. The only difference between groups will be whether CSWD is active or sham.

## 11.1 Standard physiotherapy programme for both groups

The standard physiotherapy programme will be delivered by licensed physiotherapists and will include stretching exercises, core-stabilisation exercises, postural education, and home exercise advice.

Each treatment session will include stretching of hamstrings, piriformis, and lumbar paraspinal muscles. Each stretch will be performed as three repetitions of 30 seconds. Core-stabilisation exercises will include transversus abdominis activation, bridging, and quadruped exercises, performed as two sets of 10 repetitions according to participant tolerance.

Participants will receive education on posture, ergonomics, maintaining usual activity, and adherence to home exercises. Participants will be encouraged to maintain normal activity levels but will be advised not to receive other physiotherapy or electrotherapy treatments for low back pain during the intervention period.

## 11.2 Active CSWD group

Participants allocated to the active CSWD group will receive continuous shortwave diathermy in addition to standard physiotherapy.

- Frequency: 27.12 MHz.
- Mode: continuous wave.
- Power output: 120-180 W.
- Intensity: adjusted to produce comfortable warmth without pain or discomfort.
- Duration: 20 minutes per session.
- Treatment frequency: three sessions per week for four weeks.
- Application method: two plate-type electrodes applied bilaterally over the lumbar region using the coplanar technique.
- Electrode separation: approximately 5-10 cm.
- Insulation: dry towel insulation will be used.

## 11.3 Sham CSWD group

Participants allocated to the sham CSWD group will receive sham CSWD in addition to standard physiotherapy. Participants will be positioned identically to the active CSWD group. Plate electrodes will be placed over the lumbar region for 20 minutes; however, no energy output will be delivered, and the device will remain at 0 W. Participants will be informed that warmth perception varies between individuals to support blinding credibility.

# 12. Intervention standardisation and adherence

All physiotherapists involved in treatment delivery will receive structured training before study initiation using a standardised treatment manual. The training will include CSWD safety procedures, electrode placement, sham procedures, exercise delivery, participant education, and adverse event documentation.

Treatment fidelity will be monitored using standardised treatment checklists, periodic site supervision, and trial steering committee oversight.

Attendance will be recorded at each treatment session. Participants who complete at least 80% of scheduled treatment sessions will be considered adherent for per-protocol analysis.

# 13. Outcome measures

## 13.1 Primary outcomes

1. Back pain intensity measured using a 0-10 numerical rating scale.
2. Leg pain intensity measured using a 0-10 numerical rating scale.
3. Activity limitation measured using the Oswestry Disability Index.

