# 16. Sample size calculation

The sample size was calculated based on detecting a clinically meaningful between-group difference of 2 points on the 0-10 numerical rating scale for pain intensity. The assumptions were: standard deviation of 3, power of 80%, and two-sided alpha of 0.05.

This required 86 participants per group. Allowing for 20% attrition, the final target sample size is 208 participants, with 104 participants per group.

The study is powered based on the primary outcome of pain intensity. Although repeated measurements will be collected over time, the planned linear mixed-effects modelling approach will account for within-subject correlation and is expected to increase statistical efficiency.

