# 17. Statistical analysis

All analyses will follow the intention-to-treat principle.

Primary outcomes will be analysed using linear mixed-effects models. The models will include group, time, and group-by-time interaction as fixed effects, and participant as a random effect.

Continuous secondary outcomes will be analysed using similar mixed-effects models where appropriate. Categorical outcomes will be analysed using logistic regression or chi-square tests. Post-hoc comparisons will be adjusted using Bonferroni correction where appropriate.

Missing data will be handled using Multiple Imputation by Chained Equations under the assumption that data are missing at random. The imputation model will include baseline outcomes, treatment allocation, and relevant demographic variables. At least 20 imputations will be generated.

To assess potential attrition bias, baseline characteristics of participants who complete the study and those who do not will be compared.

A per-protocol sensitivity analysis will include participants who complete at least 80% of treatment sessions. All statistical analyses will be conducted using SPSS version 29.0 or later. Statistical significance will be set at p < 0.05.

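### Leg pain is a primary outcome analysed in everyone randomised, although people without leg pain are eligible, so its mean difference is diluted by an unknown share

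*Protocol*

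**What the plan says.** - **Outcome.** Protocol section 13.1 names three primary outcomes: back pain, leg pain and the Oswestry Disability Index. The leg-pain entry reads "Leg pain intensity measured using a 0-10 numerical rating scale" and names no population.
- **Eligibility.** Section 7.1 accepts "Pain located between the 12th rib and inferior gluteal fold, with or without referred leg pain", and section 6 repeats that "Participants may have low back pain with or without referred leg pain". The only severity threshold is "Average baseline pain intensity of at least 4 on a 0-10 numerical rating scale". No minimum is set for leg pain.
- **Randomisation.** Section 9: "Permuted block randomisation with block sizes of 4 and 6 will be used and stratified by centre". Presence of leg pain is not a stratification factor.
- **Analysis.** Section 17: "All analyses will follow the intention-to-treat principle", and "Primary outcomes will be analysed using linear mixed-effects models", with group, time and their interaction as fixed effects and participant as a random effect. No section limits the leg-pain analysis to people who have leg pain. The qualifier on applicability in section 14 concerns what is collected at each visit and defines no analysis population.
- **Target difference.** Section 16 is built on a "clinically meaningful between-group difference of 2 points on the 0-10 numerical rating scale for pain intensity", and does not say whether back or leg pain is meant.

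**The concern.** The primary objective in section 2.1 is to reduce pain intensity and disability. A participant who enters with leg pain 0 has no leg pain to reduce: the score can only stay at 0 or rise. Such a participant still counts fully in a primary analysis of leg pain. The average over everyone then mixes the effect in people with leg pain with a difference near zero in the rest.

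Two things are at stake. First, the estimate shrinks in proportion to the share without leg pain, so its size depends on the case mix recruited as well as on the treatment. Second, precision does not improve enough to compensate, so one of the three primary outcomes may lose power. The distortion is towards no effect. The risk is a missed or understated benefit, not a false positive.

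**Working it through.** **Inputs from the protocol.** Difference 2 points, SD 3, two-sided alpha 0.05, 80% power, 86 per group before attrition, 104 per group after allowing for 20% attrition (section 16). Evaluable number: 104 × 0.8 = 83.2, taken as 83 per group.

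**The plan's own figure.** The usual two-means formula with difference 2 and SD 3 gives 36 per group (37 with the t distribution), not 86. That discrepancy is a separate matter. It matters here only because 83 per group gives about 99% power for an undiluted 2-point difference, and this reserve absorbs part of the dilution.

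**Assumptions not in the protocol.**
- The share p with leg pain at baseline is 30–60%, with 70% as a check.
- The effect is 2 points in people with leg pain and zero in the others, who stay at 0.
- SD is 3 among people with leg pain, for follow-up and for change scores alike.
- Mean scores in those with leg pain (sham versus active) are 4.5 versus 2.5 at follow-up; for change from baseline, −1 versus −3 or −2 versus −4.

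**Formulas.**
- Full-sample difference = 2p.
- Variance in an arm with mean m among those with leg pain = p × 9 + p(1 − p) × m². Average the two arms and take the square root for the SD.
- Full-sample power: two-sample t-test with 83 per group, standard error SD × √(2/83).
- Restricted power: the same test with 83p per group, difference 2, SD 3.

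**Worked example, p = 0.5** (difference 1.0).
- Follow-up scores: sham 4.5 + 0.25 × 20.25 = 9.56; active 4.5 + 0.25 × 6.25 = 6.06; mean 7.81, SD 2.80. Standard error 2.80 × 0.155 = 0.43. Power 63%.
- Change −2 versus −4: variances 5.50 and 8.50, mean 7.00, SD 2.65, power 68%.
- Change −1 versus −3: variances 4.75 and 6.75, mean 5.75, SD 2.40, power 76%.
- Restricted: 41.5 per group, standard error 3 × √(2/41.5) = 0.66, power 85%.

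**Results.**

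| Share p | Full-sample difference | Power, follow-up 4.5 v 2.5 | Power, change −2 v −4 | Power, change −1 v −3 | Power, restricted to baseline leg pain |
|---|---|---|---|---|---|
| 30% | 0.6 | 37% | 42% | 51% | 64% |
| 40% | 0.8 | 50% | 55% | 65% | 76% |
| 50% | 1.0 | 63% | 68% | 76% | 85% |
| 60% | 1.2 | 75% | 79% | 85% | 91% |
| 70% | 1.4 | 85% | 87% | 91% | 95% |

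Higher follow-up means (5 versus 3) lower the follow-up column by about 3 to 5 points, to 81% at p = 70%. The restricted analysis has more power than the full-sample analysis at every share shown, despite its smaller number.

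**The case against.** **The planned model is not a t-test on follow-up scores.** This stands. Section 17 specifies a mixed model with a group-by-time term, and section 14 includes a baseline measurement, so the contrast is closer to a comparison of changes. That removes much of the stable difference between people with and without leg pain, and the change-score columns show power 4 to 14 points higher than the follow-up column. Repeated visits may add further efficiency. None of this alters the dilution of the estimate to about 2p.

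**The analysis set for each outcome can be left to a statistical analysis plan.** This stands in part. Such a plan may exist and is not shown, and the handling of a cluster of zeros belongs there, so the fit of a linear model is not counted against the protocol. But which outcome is primary, who is eligible and that all analyses follow intention to treat are fixed in the protocol, and together they put people with no leg pain into a leg-pain primary analysis.

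**Intention to treat forbids a restriction.** It does not. A subset defined by a measurement taken before randomisation, and analysed as randomised, keeps the randomised comparison.

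**Stronger readings that the protocol does not support.**
- A reader might infer that the leg-pain result is likely to be a false negative. That depends on p, which is not given. Most of the full-sample figures above are at or over 50%, and all exceed 80% at p = 70%.
- A reader might say the result cannot be judged against the 2-point target. Section 16 sets that target for pain intensity without naming leg pain.
- A reader might take the entry threshold to admit someone with severe leg pain and mild back pain. The surrounding criteria define low back pain by location, so back pain is the natural reading. At most this is a separate point of wording.

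**Conclusion.** The point holds, with moderate confidence. The protocol combines an unrestricted leg-pain primary outcome with eligibility that does not require leg pain, and nothing in it corrects for this. The full-sample difference is then roughly p times the effect in people with leg pain: 0.6–1.2 points for a true 2-point effect if p is 30–60%.

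The loss of power is conditional. Compared with restricting to baseline leg pain, it is about 13 to 27 percentage points at p = 30% (64% against 37–51%) and 6 to 16 points at p = 60% (91% against 75–85%). From about p = 70% upwards, full-sample power stays above 80%, helped by a sample larger than the stated inputs require.

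The figures rest on the assumed share, the assumed means, SD 3 in those with leg pain, and no treatment effect on new leg pain. The direction of the dilution needs only the last of these and that some participants start at 0.

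The flaw does not require leg pain to lose its primary status. Restricting the analysis population removes the dilution by itself, and whether leg pain stays primary is the sponsor's choice.

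**What to change.** In section 13.1, define the leg-pain outcome in all randomised participants with leg pain at baseline, for example an NRS of at least 1 recorded before randomisation. In section 17, state that this population is analysed as randomised with the planned mixed model, and that the full-sample leg-pain analysis is supportive, so that new-onset leg pain is still reported.

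**Cost.** The change is wording in two sections. Section 9 already places the baseline assessment before the envelope is opened, and section 14 already schedules pain intensity at baseline, so no visit is added. The site must make sure that the baseline leg-pain score is recorded as its own item. Section 5 states that nobody had been enrolled at submission, so the change can be made before data exist.

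**Downside.** Leg pain is estimated in fewer people, and that number is not fixed in advance: about 25 to 50 evaluable per group at shares of 30–60% (83 × 0.3 to 83 × 0.6). At shares of 30–40% even the restricted analysis has only 64–76% power for 2 points.
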